## **1. Introduction**

Building Blocks Nutritionals (BBN), LLC has developed an infant formula for term infants that more closely resembles the composition of human milk than other commercially available infant formula products. The purpose of this randomized, controlled, double-blind study is to demonstrate that the BBN formulation meets nutritional requirements and supports age-appropriate growth of healthy term infants. The study background, design and subject assessments are described in the study protocol, BBN-IF-001.

The statistical methods to be implemented during the analyses of data collected within the scope of this study will be outlined in this document. The purpose of this plan is to provide specific guidelines from which the statistical analysis will proceed. Any deviations from this plan will be documented in the clinical study report.

## **2. Study Rationale and Objectives**

### **2.1. Study Rationale**

Human milk (HM) is universally considered the gold standard for infant feeding. HM is a dynamic, multi-faceted fluid containing nutrients and bioactive factors needed for infant health and development. If an infant cannot be breastfed, the American Academy of Pediatrics recommends infant formula as the next best feeding alternative. A goal of infant formula development is to mimic HM in both nutrient composition as well as physiologic outcomes. For years, infant formulas have not been able to provide many of the bioactive factors found in HM. With a goal of providing infants who receive infant formula a nutritional product closer in composition to HM, improvements in infant formula composition are warranted. This study is designed to evaluate the ability of BBN-001 with osteopontin (OPN) and BBN-102 without OPN to support age-appropriate growth in healthy term infants.

Analyses of BBN-001 w/ OPN compared to the Brand Formula and BBN-102 w/o OPN compared to the Brand Formula will occur separately depending on finalization of Generally Recognized as Safe (GRAS) approval of specific ingredients in BBN-001 w/ OPN Formula. This statistical analysis plan will only compare the efficacy and safety of BBN-102 w/o OPN with the Brand Formula.

## **2.2. Study Objectives**

### **2.2.1. Primary Efficacy Objective**

The primary efficacy objective is to compare the growth of infants randomized to the experimental infant formula for term infants (BBN-102 w/o OPN) versus growth of infants randomized to a commercially available term infant formula (Brand Formula).

### **2.2.2. Secondary Efficacy Objective**

The secondary efficacy objective is to compare the formula intake volume between the formula groups (BBN-102 w/o OPN vs Brand Formula).

### **2.2.3. Exploratory Objective**

The exploratory objective is to compare the markers of inflammation (tumor necrosis factor-alpha, interleukin 2, 4, 5, 6, 8, 10, 12, 13 & 17, interleukin 2 receptor, interleukin 1 beta, and interferon gamma) between the formula groups (BBN-102 w/o OPN vs Brand Formula).

### **2.2.4. Primary Safety Objective**

The primary safety objective is to compare the frequency of adverse events (AEs) between the formula groups (BBN-102 w/o OPN vs Brand Formula).

### **2.2.5. Secondary Safety Objective**

The secondary safety objective of this study is to compare the gastrointestinal tolerance (stool composition, bowel movements, stool consistency, gas, fussiness, and ICQ scales) between the formula groups (BBN-102 w/o OPN vs Brand Formula).

## **3. Study Design**

This study is a randomized, controlled, double-blind, study of healthy term formula fed (FF) infants. In the first phase of the study, FF infants will be randomized to receive either a new infant formula formulated for healthy term infants (BBN-001 w/ OPN) or a commercially available infant formula for healthy term infants (Brand Formula). After completion of the first phase, the second phase of the study will randomize infants to receive either BBN-102 w/o OPN or Brand Formula. Infants will consume the formula for a total of 16-weeks; infant growth, serum markers of inflammation, and tolerance to the formulas will be assessed throughout the four-month study period.

The study duration from Day 1 through the EOS visit is approximately 120 days. Each infant will be screened for all inclusion and exclusion criteria. If an infant complies with all inclusion and exclusion criteria and the parent(s)/guardian(s) sign the IRB-approved

Informed Consent Form (ICF), the infant will be randomized to receive a study formula and assigned a unique subject number. If the infant does not comply with one or more of the inclusion or exclusion criteria, the infant will be defined as a screen failure.

Nine visits are scheduled at 15-day intervals with a 3-day visit window.

A flowchart of the study visits is included on the following page.

## 4. FLOWCHART

Shaded columns indicate visit occurs at study site

### 4.1. Study Flowchart

| Study Visit                                       | 1 | 2  | 3  | 4  | 5  | 6  | 7  | 8   | 9   |
|---------------------------------------------------|---|----|----|----|----|----|----|-----|-----|
| Study Day                                         | 0 | 15 | 30 | 45 | 60 | 75 | 90 | 105 | 120 |
|                                                   |   | ±3 | ±3 | ±3 | ±3 | ±3 | ±3 | ±3  | ±3  |
| Informed consent                                  | X |    |    |    |    |    |    |     |     |
| Inclusion/Exclusion criteria                      | X |    |    |    |    |    |    |     |     |
| Demography                                        | X |    |    |    |    |    |    |     |     |
| Randomization                                     | X |    |    |    |    |    |    |     |     |
| Infant feeding history                            | X |    |    |    |    |    |    |     |     |
| Physical Exam                                     | X |    |    |    |    |    |    |     |     |
| Medical History                                   | X | X  | X  |    | X  |    | X  |     | X   |
| Anthropometry                         | X | X  | X  |    | X  |    | X  |     | X   |
| Stool Characteristics and Tolerance Questionnaire | X | X  | X  | X  | X  | X  | X  | X   | X   |
| Infant Characteristics Questionnaire (ICQ)        | X | X  | X  |    | X  |    | X  |     | X   |
| 3-day Formula/Diet Record             | X | X  | X  |    | X  |    | X  |     | X   |
| Blood Collection                      |   |    |    |    |    |    |    |     | X   |
| Dispense stool collection kit         |   |    |    |    |    |    | X  |     |     |
| Stool Collection                      |   |    |    |    |    |    |    |     | X   |
| Telephone contact                     | X |    |    | X  |    | X  |    | X   |     |
| Concomitant Medications                           | X | X  | X  | X  | X  | X  | X  | X   | X   |
| Adverse events                                    | X | X  | X  | X  | X  | X  | X  | X   | X   |
| Dispense and collect study formula                | X | X  | X  |    | X  |    | X  |     | X   |

Anthropometry includes assessment of weight, length, and head circumference (see Appendix C in protocol for procedure details).

Initial 3-day Formula/Diet Record will be recorded for 3 days following the first study visit. Remainder of 3-day Formula/Diet Records will be recorded for 3 days prior to each subsequent scheduled study visit.

Blood collection to assess markers of inflammation (tumor necrosis factor-alpha, interleukin 2, 4, 5, 6, 8, 10, 12, 13, & 17; interleukin 2 receptor, interleukin 1 beta, and interferon gamma) and albumin.

Stool collection to assess stool composition. Stool collection supplies will be distributed to parents at Visit 7 for collection of all stools in the 3 days just before Visit 9. The stool collection kit is returned at Visit 9.

Initial telephone contact will occur 3 days after enrollment to check compliance with study feeding and inquire about subject well-being. Remainder of telephone contacts will occur mid-way between clinic visits. Telephone contact notes will be recorded in the study subject's medical record.

## 5. Determination of Sample Size

Approximately 352 healthy term infants will be enrolled in both phases of the study to complete a minimum of 264 evaluable infants.

Formula fed infants will be randomly allocated to one of the three study formulas (BBN-001 w/ OPN, BBN-102 w/o OPN, Brand Formula) via IWRS (Interactive Web-Based Randomization System). Randomization will be blocked by formula group and stratified by infant sex to allow for balance in the number of males and females in each formula group.

Sample size estimation is based on a test for non-inferiority of the primary efficacy endpoint, mean daily weight gain (g/day), over a 16-week study period. Mean daily weight gain will be compared between formula groups by the calculation of the 95% confidence interval on the difference between the two means. A non-inferiority margin of -3 g/day is set for the difference in mean daily weight gain for the formula-fed groups. Non-inferiority is established, at the one-sided  $\alpha=0.025$  significance level, if the lower limit of the two-sided 95% confidence interval on the difference between the two least square means (BBN – Brand) is above -3 g/day.

For phase one of the study, sample size estimation is based on a test for non-inferiority between BBN-001 w/OPN Formula and Brand Formula. Assuming a standard deviation in mean daily weight gain of 5.6 g/day (Nelson et al., 1989) and 80% power, 90 subjects per group (180 total subjects) will be sufficient to demonstrate non-inferiority (one sided  $\alpha=0.025$ ). Assuming a 25% attrition rate, a total of 256 subjects will be enrolled in the BBN-001 w/ OPN Formula and Brand Formula groups.

For phase two of the study, sample size estimation is based on a test for non-inferiority between BBN-102 w/o OPN Formula and Brand Formula. A blinded interim analysis of 81 subjects who completed 16 weeks of the study was performed in phase one of the study to estimate the standard deviation of mean daily weight gain (g/day). Based on this analysis, it is assumed that the standard deviation in mean daily weight gain is 6.0 g/day. Assuming this standard deviation and approximately 90% power, approximately 168 subjects (64 in the BBN-102 w/o OPN Formula group and 104 in the Brand Formula group) will be sufficient to demonstrate non-inferiority (one-sided  $\alpha=0.025$ ). Assuming a 25% attrition rate, a total of approximately 96 subjects will be enrolled in phase two.

The plan is to use the 129 subjects randomized to Brand Formula in the first phase of the study. Assuming a 25% attrition rate, we estimate 96 subjects will meet the Per Protocol (PP) population criteria. This data will remain blinded through the enrollment of phase

two of the study. In phase two of the study, infants will be randomized to Brand Formula or BBN-102 w/o OPN in a 1:8 ratio. Assuming a 25% attrition rate and to obtain at least 90% power, approximately 10 subjects randomized to Brand Formula and 86 subjects randomized to BBN-102 w/o OPN Formula will be enrolled in phase two of the study. With the addition of the 129 subjects from phase one of the study, there will be approximately a total of 139 subjects enrolled in the Brand Formula group and 86 subjects in the BBN-102 w/o OPN Formula group. Infants will be stratified by sex to achieve balance of males and females within each formula group.

At the conclusion of the study, a post-hoc power analysis on weight gain will be conducted.

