### **14.2 Statistical Power and Sample Size Considerations**

In phase one, assuming a standard deviation in weight gain of 5.6 g/d (Nelson et al., 1989) and 80% power, 90 subjects per group (180 total) will be sufficient to demonstrate non-inferiority (one sided alpha = 0.025). Assuming a 25% attrition rate, a total of 256 subjects will be enrolled in this trial. Within each formula group, infants will be balanced by sex (equal number of males and females in each formula group). At the conclusion of the study, a post-hoc power analysis on weight gain will be conducted.

In phase two, the sample size for this study will be based on a non-inferiority test comparing weight gain velocity between Brand Formula and BBN-102 w/o OPN at Week 16. A non-inferiority margin of 3 g/d is set for the difference in weight gain for the two formula-fed groups (BBN-001 w/ OPN and BBN-102 w/o OPN).

A blinded interim analysis of 81 subjects who completed 16 weeks of the study was performed in phase one of the study to estimate the standard deviation of weight gain. Based on this analysis, it is assumed that the standard deviation in weight gain is 6.0 g/d. Assuming this standard deviation in weight gain of 6.0 g/d and approximately 90% power, approximately 168 (104 in the Brand Formula group and 64 in the BBN-102 w/o OPN group) will be sufficient to demonstrate non-inferiority (one-sided alpha = 0.025). Assuming a 25% attrition rate, approximately a total of 96 subjects will be enrolled in phase two of this trial.

The plan is to use the 129 subjects randomized to Brand Formula in phase one of the study, assuming a 25% attrition rate and 96 subjects meet the Per Protocol population criteria. This data has and will remain blinded through the enrollment of phase two of the study. In phase two of the study infants will be randomized to Brand Formula or BBN-102 w/o OPN in a 1:8 ratio. Assuming a 25% attrition rate and to obtain approximately 90% power, approximately 10 subjects randomized to Brand Formula and 86 subjects randomized to BBN-102 w/o OPN will be enrolled in phase two of the study. With the addition of the 129 subjects from phase one of the study, there will be approximately a total of 139 subjects enrolled in the Brand Formula group and 86 subjects enrolled in the BBN-102 w/o OPN group. Infants will be stratified by sex to achieve balance of males and females within each formula group.

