## 5. Determination of Sample Size

Approximately 256 healthy term infants (128 per group, 64 per gender per group) will be enrolled to complete a minimum of 180 evaluable infants (90 per group, 45 per gender per group).

Formula fed infants will be randomly allocated to one of the two study formulas

(Formula A or B) via IWRS (Interactive Web-Based Randomization System).

Randomization will be blocked by formula group and stratified by infant sex to allow for an equal number of males and females in each formula group.

Sample size estimation is based on the primary endpoint, weight gain velocity (g/d) over a 16-week study period.

Assuming a standard deviation in weight gain of 5.6 g/d (Nelson et al., 1989) and 90% power, 90 subjects per group (180 total) will be sufficient to demonstrate equivalence (one sided  $\alpha = 0.025$ ). Assuming a 25% attrition rate, a total of 256 subjects will be enrolled in this trial, 128 males and 128 females.

Based on discussions with regulatory agencies and internal discussions we have decided to base the results on non-inferiority. A non-inferiority margin of 3 g/d is set for the difference in weight gain for the two formula-fed groups. Based on a standard deviation in weight gain of 6.0 g/d from the interim analysis and 90 subjects per group (180 total), the power for non-inferiority is greater than 90% and is sufficient for the analyses planned.

At the conclusion of the study, a post-hoc power analysis on weight gain will be conducted.

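### Phase-one power is printed as 80%, but the stated inputs give about 95% at no true difference; in phase two, only the SAP's at-least-90% wording goes beyond its inputs (about 88%)

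*Supplement*

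**What the plan says.** SAP V4 section 5 sizes both phases on a non-inferiority comparison of two means: "A non-inferiority margin of -3 g/day is set for the difference in mean daily weight gain". The lower limit of the two-sided 95% confidence interval for BBN minus Brand must lie above that value, which is a one-sided test at 0.025.

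**Phase one.** The standard deviation comes from published reference growth data ("Assuming a standard deviation in mean daily weight gain of 5.6 g/day"), and the section concludes that "80% power, 90 subjects per group (180 total subjects) will be sufficient to demonstrate non-inferiority". Protocol v5.2 agrees in its synopsis and in section 14.2: "80% power, 90 subjects per group (180 total) will be sufficient to demonstrate non-inferiority (one sided alpha = 0.025". Neither document states the true difference assumed.

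**Phase two.** The standard deviation is raised to 6.0 g/day after a blinded look at 81 completers. Both documents describe 104 Brand and 64 BBN-102 evaluable infants as giving approximately 90% power. SAP V4 section 5 then turns to enrolment: "Assuming a 25% attrition rate and to obtain at least 90% power, approximately 10 subjects randomized to Brand Formula and 86 subjects randomized". Adding the 129 Brand infants from phase one makes 139 Brand and 86 BBN-102 enrolled. For this same target the protocol (synopsis and 14.2) claims only approximately 90%.

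**Phase-one SAP.** This separate plan (V2, October 2019), also in its section 5, takes 90 per group and a standard deviation of 6.0 and says that "the power for non-inferiority is greater than 90% and is sufficient for the analyses planned". For the earlier equivalence test at 5.6 it gives 90%.

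**The concern.** Phase-one power cannot be 80% at a standard deviation of 5.6 and above 90% at 6.0 when the group size, margin and alpha are the same, because a larger standard deviation can only lower power. The 80% still stands in the latest protocol and in SAP V4, both of which now describe the test as non-inferiority.

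The phase-two text uses two strengths of claim for one design: approximately 90% and at least 90%.

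No test, margin or sample size turns on these sentences. What is at stake is whether a reader can tell what true difference the trial was built to tolerate. SAP V4 section 5 also promises a post-hoc power analysis, which would be set beside a planned figure that its own inputs do not give.

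**Working it through.** **Inputs**

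- Margin 3 g/day, one-sided alpha 0.025 (z = 1.960): SAP V4 section 5; protocol 14.2 for alpha.
- Phase one: SD 5.6, 90 per group.
- Phase two: SD 6.0, 104 against 64 evaluable; 139 and 86 enrolled with 25% attrition.
- True difference: not given. I take 0 as my assumption.

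Formula, unadjusted comparison: SE = SD × √(1/n₁ + 1/n₂); power = Φ(3/SE − 1.960).

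**Phase one: trying to reproduce 80%**

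- SE = 5.6 × √(2/90) = 0.835.
- Power = Φ(3/0.835 − 1.960) = Φ(1.634) = 94.9% (94.7% with the noncentral t).
- Group size for 80%: 2 × (5.6 × (1.960 + 0.842)/3)² = 54.7, so 55 per group rather than 90.

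Variants with 90 per group and SD 5.6, unless noted:

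| Variant | Power |
|---|---|
| Equivalence, two one-sided tests at 0.025 | 89.8% |
| Equivalence, two one-sided tests at 0.05 | 94.9% |
| Non-inferiority, one-sided 0.05 | 97.4% |
| Non-inferiority, one-sided 0.0125 | 91.2% |
| Non-inferiority at 0.025, 96 per group (256 × 0.75 / 2) | 96.0% |

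None gives 80%. Solving backwards:

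- True deficit giving 80%: 3 − 0.835 × 2.802 = 0.66 g/day.
- SD giving 80%: 3 / (0.1491 × 2.802) = 7.18 g/day, where 0.1491 = √(2/90).

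The phase-one SAP's own figures do reproduce. Its 90% for equivalence is the 89.8% above. At SD 6.0, SE = 6.0 × 0.1491 = 0.894 and power = Φ(3.354 − 1.960) = 91.8%, which is above 90% as it says.

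**Phase two**

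- 104 against 64: SE = 6.0 × √(1/104 + 1/64) = 0.953; power = Φ(3.147 − 1.960) = 88.2% (t: 87.9%).
- Enrolment target net of attrition: 139 × 0.75 = 104.25 and 86 × 0.75 = 64.5. SE = 0.951; power = Φ(3.156 − 1.960) = 88.4% (t: 88.1%).
- For 90% with Brand held at 104, BBN-102 would need 70.5, so 71 evaluable infants by the normal formula.

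Sensitivity to the unstated difference, 104 against 64: at a true −0.5 g/day, Φ(2.5/0.953 − 1.960) = 75%; at −1.0 g/day, Φ(2.0/0.953 − 1.960) = 55%.

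**The case against.** **Approximately 90% is fair for 104 against 64.** This stands. The figure computed for those numbers is 88.2%. A reader might infer that the phase-two power fails to reproduce, as phase one does. The documents do not support that: the at-least wording occurs once, in SAP V4 section 5, and is tied to the enrolment target after attrition.

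**The planned analysis is adjusted.** The primary model (SAP V4, 6.8 and 9.1) includes sex, age at enrolment, baseline value and pooled site. With 104 against 64, 90% power needs SE = 3/(1.960 + 1.282) = 0.925, a residual SD of about 5.83. Covariates explaining about 6% of the variance would do it, since 1 − (5.83/6.0)² ≈ 0.06. This stands as a limit on how firmly the shortfall can be put. It does not rescue the wording, because the sample-size text claims no such gain and gives no correlation.

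**The 95% depends on a zero difference that the sponsor never stated.** This also stands. A reader might infer that the sponsor assumed 0, or that it built in an allowance of about 0.66 g/day. The documents support neither, so the sponsor has to say which applies.

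**Phase one is history, and the error is safe.** Largely true. Ninety per group is more than 80% power requires at no true difference, and SAP V4 compares only BBN-102 with Brand (section 2.1). That keeps the point minor, but the figure is still printed as current in both documents.

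**Conclusion.** The phase-one figure is wrong as written. The stated inputs give about 95% at a true difference of 0, some 15 points above the printed 80%, and the phase-one SAP's statement at SD 6.0 cannot be squared with 80%. The error understates power.

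For phase two there is a smaller fault of wording. At least 90% is not met by the unadjusted calculation, by less than 2 points (88.4%), and it conflicts with the approximately 90% used elsewhere in the same section and in the protocol.

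A reader might go further and conclude that phase two is underpowered and needs more infants. The documents do not support that: the gap is under 2 points before any gain from covariates.

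All of this rests on a true difference of 0 and an unadjusted comparison of two means. The first is my assumption, for the sponsor to confirm.

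**What to change.** - **Phase one** (protocol v5.2 synopsis and 14.2; SAP V4 section 5): restate power as about 95% with SD 5.6 and a true difference of 0, if 0 was the assumption. If it was not, keep 80% and state the non-zero difference that yields it.
- **Phase two** (SAP V4 section 5, the enrolment sentence): replace the at-least-90% claim with about 88%, for SD 6.0, true difference 0, unadjusted.
- **Both phases:** state the assumed true difference beside the margin, standard deviation and alpha.

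This costs a text correction in two documents. Enrolment and the analysis stay as they are. The phase-two figure reads slightly less favourably and the phase-one figure more so.

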## 6. Statistical Methods

The statistical analyses will be reported using summary tables, figures and listings (TFLs). Numbering for TFLs will be based on the recommended numbering convention provided by the International Conference on Harmonisation. Unless noted otherwise, all statistical tests will be two-sided with a significance level of  $\alpha = 0.05$ . Tests will be declared statistically significant if the calculated p-value is  $\leq 0.05$ . Continuous variables will be summarized with means, standard deviations, medians, minimums and maximums. Categorical variables will be summarized by counts and percent of subjects in corresponding categories. Missing values are not considered for percent calculations, unless stated otherwise. In those cases, footnotes will specify the percent basis. All summary tables will be presented by formula received. Select baseline tables may also include a total summary.

Individual subject data obtained via the electronic data capture (EDC) system and from external vendors will be presented in by subject listings.

The analyses described in this plan are considered *a priori*, in that they have been defined prior to the blind being broken and the database locked. Any analysis performed after breaking the blind will be considered post-hoc and exploratory. Post-hoc analyses will be labeled as such on the output and identified in the CSR.

All analyses and tabulations will be performed using SAS® version 9.4 or higher. Tables and listings will be presented in pdf and rtf format. Upon completion, all SAS programs will be validated by an independent programmer. The validation process will be used to confirm that statistically valid methods have been implemented and that all data manipulations and calculations are accurate. Checks will be made to ensure accuracy,

consistency with this plan, consistency with tables and consistency between tables and corresponding data listings.

